# Babies Living Safe & Smokefree: randomized controlled trial of a multilevel multimodal behavioral intervention to reduce low-income children’s tobacco smoke exposure

**DOI:** 10.1186/s12889-017-4145-7

**Published:** 2017-03-14

**Keywords:** Secondhand tobacco smoke, Randomized controlled trial, WIC, Prevention, Smoking cessation, Community health services, Multilevel

## Abstract

**Background:**

Addressing children’s tobacco smoke exposure (TSE) remains a public health priority. However, there is low uptake and ineffectiveness of treatment, particularly in low-income populations that face numerous challenges to smoking behavior change. A multilevel intervention combining system-level health messaging and advice about TSE delivered at community clinics that disseminate the Special Supplemental Nutrition Program for Women, Infants and Children (WIC), combined with nicotine replacement and intensive multimodal, individual-level behavioral intervention may improve TSE control efforts in such high-risk populations.

**Methods/Design:**

This trial uses a randomized two-group design with three measurement points: baseline, 3-month and 12-month follow-up. The primary outcome is bioverified child TSE; the secondary outcome is bioverified maternal quit status. Smoking mothers of children less than 6 years old are recruited from WIC clinics. All participants receive WIC system-level intervention based on the “Ask, Advise, Refer (AAR)” best practices guidelines for pediatrics clinics. It includes training all WIC staff about the importance of maternal tobacco control; and detailing clinics with AAR intervention prompts in routine work flow to remind WIC nutrition counselors to ask all mothers about child TSE, advise about TSE harms and benefits of protection, and refer smokers to cessation services. After receiving the system intervention, mothers are randomized to receive 3 months of additional treatment or an attention control intervention: (1) The multimodal behavioral intervention (MBI) treatment includes telephone counseling sessions about child TSE reduction and smoking cessation, provision of nicotine replacement therapy, a mobile app to support cessation efforts, and multimedia text messages about TSE and smoking cessation; (2) The attention control intervention offers equivalent contact as the MBI and includes nutrition-focused telephone counseling, mobile app, and multimedia text messages about improving nutrition. The control condition also receives a referral to the state smoking cessation quitline.

**Discussion:**

This study tests an innovative community-based, multilevel and integrated multimodal approach to reducing child TSE in a vulnerable, low-income population. The approach is sustainable and has potential for wide reach because WIC can integrate the tobacco intervention prompts into routine workflow and refer smokers to free evidence-based behavioral counseling interventions, such as state quitlines.

**Trial registration:**

Clinicaltrials.gov NCT02602288. Registered 9 November 2015.

## Background

Children’s tobacco smoke exposure is a leading cause of disease in children and is linked to behavioral problems. [1–3] Babies and preschoolers are at particular risk for tobacco smoke exposure (TSE) because of their dependence on others to avoid exposure. Residential smoking is the main source of child TSE, with maternal smoking having a primary effect on young children [4]. Therefore, addressing child TSE and maternal smoking remains a public health priority [5]. Because TSE is very high among impoverished children [2, 6], and poverty is linked to higher smoking rates among women of childbearing age [7, 8], effective TSE intervention targeting low-income maternal smokers is needed. Evidence-based treatments are available, but uptake of these treatments remains low in impoverished populations [9]. Community health systems serving low-income communities, such as the Special Supplemental Nutrition Program for Women, Infants and Children (WIC), could facilitate intervention uptake in this high-risk population.

It is well established that smoking is influenced by multiple factors [2] including physical addiction, learned behaviors and social factors, that interact with one another and maintain their influence across both temporal and physical contexts [10, 11]. However, most efforts to address maternal smoking in community settings typically use just a “single-level” approach [12] that attempts to address factors at either the individual, social, or environmental level of influence. Such approaches have limited effectiveness in changing smoking behavior [13]. Therefore, testing innovative multimodal, multilevel TSE interventions could advance the field [14, 15]. Such approaches could address a wider array of factors that maintain smoking behavior and increase the odds of quitting relative to any single-level intervention [16]. Multilevel approaches could also boost intervention dosage through multiple message channels across levels of influence, thereby increasing the potency of intervention. While different sources of messaging may differentially influence knowledge, attitudes and motivation to change [17], systematic multilevel messaging could produce interactive effective across levels of influence to augment motivation and behavior change [18]. However, multilevel approaches are underutilized [19], particularly when addressing maternal smoking and child TSE. Underutilization may be due to resource and logistics challenges in community clinic settings – constraints this trial attempts to overcome.

The Babies Living Safe and Smokefree (BLiSS) program addresses the current limitations to implementing smoking interventions in community settings, such as WIC clinics, by using multiple message sources and repeated doses of intervention components across integrated treatment modalities. Informed by our successful multilevel intervention in pediatrics clinics [20–22], the impact potential of this model is high as it addresses many determinants of maternal smoking and child TSE. First, we implement a WIC system-level “Ask, Advise, Refer (AAR)” intervention that is modeled after the American Academy of Pediatrics best practices guidelines for child TSE/tobacco control in clinic [23]. Messaging at this level of intervention is designed to increase parents’ awareness about TSE harms and the benefits of TSE protections, increase parents’ motivation to change smoking behavior, and link smokers to more evidence-based treatment (e.g., quitline). Second, participants receive behavioral counseling with a proactive quitline to guide adoption and maintenance of TSE protective behaviors, self-regulation and coping skills, while providing social support for modifying smoking behavior leading to a quit attempt. Third, a mobile app, text messaging and texted educational video clips are integrated with counseling messaging to increase treatment support, engagement and dosage. Finally, participants receive eight weeks of NRT to address the physiological level of nicotine addiction.

This trial evaluates the efficacy of the BLiSS model in a sample of urban-dwelling, predominantly low-income African American maternal smokers. Targeting this population with an intervention that exceeds the intensity of standard practice is warranted because this population bears greater tobacco-related morbidity and mortality risk [2, 5] and greater challenges to changing smoking behavior compared to the general population [7]. The BLiSS intervention is framed by the Behavioral Ecological Model [15], which logically integrates biological, social and ecological concepts with principles of behavior change and posits that smoking interventions should target multiple determinants of smoking. Thus, our multilevel approach capitalizes on contingencies of reinforcement for protecting children from TSE that function reciprocally across levels of influence, including (a) a clinic system-level (e.g., meta-contingencies that promote AAR best practices and a culture within WIC clinics that encourage TSE protection norms); the interpersonal level (e.g., counselor provision of social support and guidance with problem solving during quitline sessions); and the intrapersonal level (e.g., mobile app experience that extends WIC and quitline counselor advice about TSE reduction). The BLiSS intervention model represents an innovative approach in WIC clinics that uses evidence-based clinic and multimodal behavioral treatment elements informed by the literature, our previous research and theory [15, 20, 21, 24–26].

### Aims and hypotheses

Aim 1: Test the hypothesis that a program integrating a WIC system-level “AAR” intervention with an intensive multimodal behavioral intervention (AAR + MBI) will be more effective in reducing child TSE (primary outcome) than a WIC system AAR plus an attention control intervention (AAR + Control). *Hypothesis 1:* Compared with AAR + Control children, those in the AAR + MBI condition will have significantly greater reductions in parent-reported daily TSE and child urine cotinine from baseline to 3- and 12-month follow-up.

Aim 2: Test the hypothesis that the multilevel AAR + MBI will be more effective at increasing maternal quit rates (secondary outcome) than AAR + Control. *Hypothesis 2:* Compared with the control group, mothers in AAR + MBI will have a significantly greater bioverified, 7-day point prevalence quit rate at 3- and 12-month follow-up.

Aim 3: Test hypotheses that changes in theoretically important variables will mediate the effects of AAR + MBI on child TSE and parent smoking outcomes. *Hypothesis 3*: Compared with parents in the AAR + Control condition, parents in the AAR + MBI condition will evidence greater increases in TSE protective behaviors, social support, urge management coping skills, and self-efficacy related to protecting child from TSE and quitting smoking from baseline to 3-month follow-up. In turn, these changes in mediator variables will account for between-group differences in TSE and cessation outcomes at month 12 (e.g., change in child cotinine from baseline to 12-month follow-up).

Aim 4: Explore factors that may influence outcomes and moderate intervention effects, including presence of other smokers at home, nicotine dependence, depressive symptoms, weight concerns, and intervention dosage as measured by quitline, NRT, and app usage.

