#### Nicotine replacement therapy starter and instructions

NRT products will be provided to participants (specifically, nicotine gum, lozenge or patch). NRT is FDA approved for smoking cessation interventions and available over the counter. Following best-practice guidelines and practices implemented by state quitlines with low-income clients [32, 40], we will mail participants up to 8-weeks of free NRT prior to their quit day. Project quitline counselors will give advice on NRT use based on guidelines including benefits and harms, safe use and disposal.

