#### Mediators

Four variables will be assessed as potential mediators: (a) Parental-reported exposure protection (PREP) behaviors are measured with self-report items used in our previous research and reflected in a recent meta-analysis. We operationalize PREP behavior in two measures: (1) families’ current home smoking policy (0 = no restrictions to 4 = total indoor ban); and (2) the sum of 10 PREP behaviors (e.g., move child away from others’ smoking). (b) Support for TSE protection and smoking cessation will be measured using a modified short form of the Partner Interaction Questionnaire. The modified measure, used in our previous multilevel trial [20], assesses perceived intervention staff support to participants for promoting TSE reduction and cessation (α = .91). (c) Self efficacy of smoking behavior change will be measured using the Smoking Cessation Self-Efficacy Scale (α = .90) and a parallel form (α = .90) we developed [20] to assess self-efficacy in reducing child TSE. (d) Urge management and coping will be assessed using the Urge Management Coping Skills measure [20] based on cognitive and behavioral coping strategies identified by O’Connell (α = .87).

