#### Process measures and treatment fidelity

Intervention processes will be assessed in both conditions with multiple methods and at each time point and intervention level: WIC clinic AAR implementation (e.g., participant reports of advice received; WIC counselor report of attitudes and practices), telephone counseling (e.g., counselor reports of attendance, duration, participant engagement), NRT utilization (e.g., participant-reported compliance), and mobile app usage (e.g., pushed data reflecting frequency of launching and using specific features).

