### Analytic plan

The predictor is intervention group (AAR + MBI vs. AAR + Control) and the two endpoints include child exposure (continuous primary outcome) and parent cessation (dichotomous secondary outcome). Primary analyses will use an intention-to-treat approach and missing data will be addressed using multiple imputation. In sensitivity analyses, we will perform complete case analyses and investigate the impact of data that is potentially missing not at random. We will compare child cotinine change scores between intervention arms using multilevel random-effects linear regressions in which we include randomization arm as a fixed effect and WIC clinic as a random intercept to account for potential clustering within clinic. Potential confounders (e.g., nicotine dependence) will be added as covariates as necessary. We will use multiple logistic regressions with random intercepts for clinic to compare bioverified self-reported quit status (yes/no) between randomization arms at 3 and 12 months. To investigate mediation pathways, we will use a structural equation approach with change in cotinine levels and parent quit status as the outcomes. We will ensure that the intervention is associated with the potential mediators (e.g., self-efficacy) and that the mediators are associated with the outcomes. We will also use cluster-adjusted bootstrap standard errors for assessment of the mediated effect in which the variables are measured in a temporal ordering consistent with a causal pathway. For moderation analyses, we will use random-effects multiple regression modeling the change in cotinine levels and parent quit status, using confounding variables as necessary.

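### The Aim 3 mediator list omits NRT use, which the trial supplies only to the MBI arm, so part of any NRT effect can be credited to urge coping or self-efficacy

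*Protocol article*

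**What the plan says.** Under Aims and hypotheses, Hypothesis 3 predicts that MBI parents will show "greater increases in TSE protective behaviors, social support, urge management coping skills, and self-efficacy related to protecting child from TSE and quitting smoking" by month 3, and that "these changes in mediator variables will account for between-group differences in TSE and cessation outcomes at month 12". The Mediators section turns this into a counted list: "Four variables will be assessed as potential mediators". These are exposure-protection behaviors (home smoking policy and a sum of ten behaviors), support, self-efficacy, and urge management and coping.

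NRT is described elsewhere. The Background assigns it a separate mechanism: "participants receive eight weeks of NRT to address the physiological level of nicotine addiction". The NRT section, which belongs to the MBI description, says "we will mail participants up to 8-weeks of free NRT prior to their quit day". Controls are not supplied with NRT by the trial; they are given the state quitline number and told that free NRT is available there.

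The section on process measures and treatment fidelity covers both conditions and includes "NRT utilization (e.g., participant-reported compliance"). Among the aims, NRT usage appears only in Aim 4, as one of the dosage measures whose influence on outcomes and moderating role are to be explored. For Aim 3 the Analytic plan states: "To investigate mediation pathways, we will use a structural equation approach with change in cotinine levels and parent quit status as the outcomes". It adds checks that arm is associated with mediator and mediator with outcome, measurement in temporal order, and cluster-adjusted bootstrap standard errors.

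**The concern.** Randomization protects the comparison of arms and the path from arm to mediator. It does not protect the path from mediator to outcome. A variable that the arm changes after randomization, and that affects both mediator and outcome, confounds that second path. NRT use is a natural candidate. The trial raises it in one arm, it may make urges easier to manage and confidence higher by month 3, and it may affect later quitting and child exposure. Baseline covariates such as nicotine dependence cannot remove this, because use of trial-supplied NRT does not exist at baseline. Association checks, temporal ordering and bootstrap standard errors do not remove it either.

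What is at stake is the attribution under Aim 3. The program is offered as a model for WIC and the state quitlines, so it matters whether skills and confidence carried the effect or whether NRT carried part of it.

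**Working it through.** **The text.** The mediator list is fixed and counted, and NRT use is not on it. NRT has its own stated route, differs by arm by design, and is measured in both arms. The omission is therefore a stated choice about the mediator set and not a detail left to an unseen analysis plan.

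**The plan's own figures.** The article gives no figure for mediation. Its only power statement is 85.7% for an effect of 0.23 in log cotinine change with 149 per group (372 × 0.80 = 297.6, rounded to 298). No SD is stated. At an assumed two-sided alpha of 0.05, 85.7% requires an SD of about 0.656, so the planned effect is about 0.23 / 0.656 = 0.35 SD. This serves only as a yardstick below.

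**Size of the misattribution.** All inputs here are assumptions; the documents give no NRT use rate and no NRT effect. Let A be arm, R be NRT use (50% in MBI, a proportion p in control), M be one mediator and Y the outcome:

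- M = 0.3·A + g·R + noise with SD 1
- Y = −0.5·R + noise with SD 1, so M has no true effect on Y

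Let v be the mean within-arm variance of R, v = [0.25 + p(1 − p)] / 2. With R left out:

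- coefficient of M given arm = −0.5·g·v / (1 + g²·v)
- arm effect on M = 0.3 + g·(0.5 − p)
- total arm effect on Y = −0.5·(0.5 − p)
- share credited to M = (arm effect on M × coefficient of M) / total arm effect

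For p = 0.05 and g = 0.3:

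- v = (0.25 + 0.0475) / 2 = 0.149
- coefficient = −0.0223 / 1.0134 = −0.022
- arm effect on M = 0.3 + 0.135 = 0.435
- indirect effect = −0.0096
- total = −0.225
- share = 4.3%

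| Control use p | g = 0.3 | g = 0.5 |
|---|---|---|
| 5% | 4.3% | 8.4% |
| 10% | 5.3% | 10.2% |
| 20% | 7.9% | 14.6% |

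The true share is 0 in every cell. A large simulation of the same model gave 4-8% and 8-14%, and returned about 0 once R was in the model. With g = 0 the share is 0 with or without R.

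**How often mediation would be declared falsely.** 2000 simulated trials per setting, 149 per group; NRT use 50% against 5%, or 60% against 10%; direct arm effect on M of 0.2 SD; no true effect of M on Y. Mediation is declared when the arm-to-mediator and mediator-to-outcome paths are both significant. The ranges cover repeated runs and both pairs of use rates.

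| NRT effect on M / on Y | NRT use omitted | NRT use in model |
|---|---|---|
| 0 / 0.5 SD | about 2% | about 2% |
| 0.3 / 0.3 SD | 4-6% | 4-6% |
| 0.5 / 0.5 SD | 8-10% | 4-6% |
| 0.8 / 0.5 SD | 15-19% | 4-6% |
| 0.8 / 0.8 SD | 30-39% | 4-6% |

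The last row is extreme. With use gaps of 45 and 50 percentage points, 0.8 SD makes NRT alone produce an arm difference of 0.8 × 0.45 = 0.36 to 0.8 × 0.50 = 0.40 SD. That is about 103% to 114% of the 0.35 SD planned effect.

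**The case against.** The strongest objection is that this is a condensed article. It names a structural equation approach without a full model, and it nowhere says that NRT use is barred from it. That holds for the covariate set. It does not hold for the mediators, which are counted and named, and NRT use is not one of them.

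Other points stand in part:

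- A reader might infer that Hypothesis 3 admits only psychosocial variables. It does not: the list includes protective behaviors and home smoking policy, and the argument about NRT concerns mainly urge coping and self-efficacy.
- A reader might infer that the mediated effects are biased upward as a matter of fact. The documents do not support this. The bias is conditional, and it is nil if NRT does not move the mediators.
- NRT use is not ignored. Aim 4 explores its influence on outcomes and its moderating role. That does not separate its pathway in the Aim 3 model.
- Controls can obtain NRT through the state quitline. This narrows the arm contrast but does not abolish it.
- Counseling and app dose are also changed by arm and measured. NRT differs in that the protocol itself gives it a distinct physiological route.
- Adjustment can err in the other direction. Counselors teach NRT use and the app sends reminders, so coping or self-efficacy may lead to NRT use within the same three months. A mediator that works wholly through NRT use would then lose its effect once NRT use is in the model. This objection stands in full and shapes the fix.

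**Conclusion.** The point holds in a limited form. The mediator set leaves out a pathway that the protocol names, supplies to one arm only and measures in both. If NRT use moves urge coping or self-efficacy and also the outcomes, part of its effect can be credited to those mediators. The size cannot be derived from the documents. Under the assumed use rates it is negligible when NRT moves mediator and outcome by about 0.3 SD each, and modest at about 0.5 SD (8-10% false mediation against 4-6%). The rates of 30% and more need 0.8 SD on both paths and should not be taken as expected.

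The tests of Aims 1 and 2 are untouched; only the attribution of mechanism under Aim 3 is affected. This is a worthwhile refinement and not a threat to the trial's main conclusions.

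**What to change.** In the Aim 3 structural equation analysis, for both cotinine change and quit status, add NRT use up to month 3 as a parallel mediator. Report:

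1. the indirect effects of the four listed mediators without NRT use in the model;
2. the same effects with NRT use in the model;
3. the indirect effect of NRT use;
4. the joint indirect effect of all mediators.

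The order of NRT use and of coping or self-efficacy within the three-month window is not established. Persistence of an effect after adjustment should therefore not be the test of a mechanism. Where the two models differ, state that the separate contributions cannot be distinguished, and rest the conclusion on the joint effect.

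The cost is one more mediator from data already planned for collection, somewhat wider intervals, and reliance on participant-reported NRT use. No trial procedure changes.

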### Procedures

Prior to initiating participant recruitment, we will conduct a formative analysis of current tobacco intervention practices among professional and paraprofessional staff who work in Philadelphia WIC clinics. This preliminary research will facilitate the translation and implementation of AAR best practices into routine WIC clinic operations and client flow that will minimize both staff and participant burden. We will then provide group training among all staff that highlights the child TSE problem and its consequences, challenges maternal smokers have in quitting smoking, and the pivotal contributing role of community health workers in tobacco control efforts. In addition, WIC nutrition counselors will receive more intensive training in the specific steps to implementing the Ask, Advice, Refer intervention.

After WIC staff refer smoking mothers with exposed children to the trial, trained research assistants will consent eligible participants and collect self-report data at baseline. Data will be collected via structured computer assisted telephone interviewing. This method reduces literacy barriers, minimizes participant burden, and maximizes data reliability. After baseline, participants are randomized to condition. A permuted blocks design was used to randomize participants stratified by clinic site and presence of other smokers in the home living with the participant (yes/no). The randomization schedule was seeded using values obtained from random.org and the project biostatistician provided the allocations to the data collection team in sealed opaque security envelopes. To preserve condition masking, participants will be randomized after baseline data collection and immediately prior to a treatment orientation home visit. During the orientation home visit, participants receive a binder with intervention materials that are relevant to their assigned intervention condition. Research staff also download a mobile app specific to condition on participants’ smartphones and show an app video tutorial, the link to which is left with the participant. The child’s urine cotinine sample is also collected during the home visit.

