### Attention control intervention: nutrition education (AAR + Control)

Trained health counselors deliver the Control intervention. Training, in-home intervention orientation, and multimodal behavioral intervention procedures parallel procedures described in the MBI arm below. However, the content of the Control behavioral intervention centers on improving nutrition on a budget, with an emphasis on reducing sugar intake and increasing fruit and vegetable consumption. The purpose of the Control group is to provide equivalent attention and contact between the two conditions while providing distinctly different behavioral intervention content. At the orientation, BLiSS staff offers participants the state quitline number including information that the quitline delivers free NRT. Staff also provide the written tool kit developed by Sesame Street Workshop, *Food for Thoughts: Eating Well on a Budget* [28], that includes nutrition guidelines, recipe cards, and colorful books with activity suggestions as well as videos about nutrition on a budget and fruit and vegetable consumption. Additionally, staff use food models to demonstrate recommended serving sizes and download the Fooducate mobile app (with video tutorial) to participant smartphones. This app scans barcodes on foods to provide real time nutrition information. Staff also provide participants with the number of the state quitline and are informed they can receive smoking cessation counseling and free NRT by calling the number. Finally, during the weeks between the orientation and 3-month end-of-treatment phone assessment, participants will receive up to 5 telephone nutrition education calls, 10 nutrition education video clips via text messaging, and inter-session text message follow-ups and appointment reminders.

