### Experimental multimodal behavioral intervention (AAR + MBI)

Prior to implementing the experimental MBI, counselors will complete a 5-day Certified Tobacco Treatment Specialists training accredited by the Association for Treatment of Tobacco Use and Dependence. An additional 30 h of training by [name] (PI) will expand counselors’ skills including (a) how to guide TSE protection efforts as part of a cognitive behavioral therapy (CBT)-framed strategy to shape parents’ behavior toward a cessation attempt; (b) how to facilitate TSE protective behaviors and smoking behavior change in the context of challenges faced by low-income parents who smoke; and (c) how to drive a counseling process that integrates support and skills training with advice that facilitates participants’ mobile app usage to extend individualized treatment beyond phone sessions. Training in CBT strategies allows for tailoring counseling to participants based on identified barriers (e.g., other smokers in the home) and catalysts (e.g., concerns for child health) of behavior change. After intensive competency-based training, counselors will refine skills in ongoing weekly supervision that includes review of fidelity monitoring feedback, discussion of current cases, and role-playing of effective session interaction.

Intervention components were informed by the current literature and our two previous smoking trials with low-income parents [20, 21, 26]. Components include integrated health messaging that parallels WIC counselor advice as well as support and guidance with skills training and problem solving that is delivered via multiple treatment modes: (a) a project quitline that provides up to 5 telephone counseling sessions during the weeks between orientation and 3-month end-of-treatment phone assessment; (b) a research-ready BLiSS mobile app; (c) print materials for the participant and their family; (d) inter-session text follow-up, reminders and support as well as scheduled educational video clips that highlight telephone session and written materials content; (d) 8 weeks of NRT and instructional support.

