#### Covariates and moderators

Four variables will be assessed as potential control variables and moderators of intervention effects: (a) Nicotine dependence will be measured with the reliable and validated Fagerström Test for Cigarette Dependence [43]. (b) Depressive symptoms will be measured with the Center for Epidemiological Studies Depression Scale, which are validated, reliable and useful in smoking studies [44]. (c) Weight concerns will be measured using a 6-item validated scale that measures general and smoking-specific weight concerns [45]. (d) Other smokers in mothers’ homes will be assessed using a standard, content valid item. Additional demographic and smoking history variables will be measured and assessed for possible association with outcomes.

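### Aim 4 treats intervention dosage as a moderator, although dosage arises after randomization, is self-selected and has no equivalent counterpart in the control arm

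*Protocol article*

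**What the plan says.** Under Aims and hypotheses, Aim 4 is to "Explore factors that may influence outcomes and moderate intervention effects". Five factors follow: other smokers at home, nicotine dependence, depressive symptoms, weight concerns, and "intervention dosage as measured by quitline, NRT, and app usage".

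The Measures section differs. Covariates and moderators states that "Four variables will be assessed as potential control variables and moderators of intervention effects" and names the first four only. Telephone counseling, NRT use and app use appear under Process measures and treatment fidelity, where "Intervention processes will be assessed in both conditions with multiple methods and at each time point and intervention level".

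On timing, Procedures says that "participants will be randomized after baseline data collection and immediately prior to a treatment orientation home visit".

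On content, the MBI arm has "a project quitline that provides up to 5 telephone counseling sessions" about smoking, the BLiSS app and mailed NRT. In the control arm, "participants will receive up to 5 telephone nutrition education calls, 10 nutrition education video clips via text messaging". Controls also get a food-scanning app and the state quitline number, through which they can obtain NRT.

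The Analytic plan states: "For moderation analyses, we will use random-effects multiple regression modeling the change in cotinine levels and parent quit status", with confounders added where needed. It describes no separate method for a variable that arises after allocation.

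**The concern.** A moderator analysis asks whether the effect of assignment differs between kinds of participant. That reading needs a characteristic that assignment cannot have influenced. Dosage fails on three counts.

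- It accrues after allocation, so it may depend on the arm.
- It is voluntary. Mothers who want to change are likely to take more calls, use more NRT and open the app more often, and also to reduce exposure more. NRT is mailed ahead of a quit day, and the app records cigarettes smoked and the quit date, so part of measured dosage may reflect change already intended or under way.
- One unit differs between arms. A further call is smoking counseling in one arm and nutrition education in the other.

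The mediator and moderator sections name no measure of motivation to quit, so covariate adjustment cannot be relied on to remove the selection. At stake is what Aim 4 can conclude. The Discussion says that app usage data will guide later work on combining mobile tools with counseling, so a confounded dose result would have some influence.

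**Working it through.** **1. Timing and content.** Randomization comes just before the orientation visit at which materials and app are handed over. All calls, NRT and app use therefore follow allocation.

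| Component | MBI | Control |
|---|---|---|
| Calls | up to 5, smoking and child exposure | up to 5, nutrition |
| App | BLiSS | food-scanning app |
| NRT | mailed by the project, up to 8 weeks | only by calling the state quitline |

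A counterpart exists for each component and is measured, but none is equivalent.

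**2. Inputs.** The Power analysis gives 372 × 0.80 = 297.6, rounded to 298, or 149 per group; this reproduces. The article states no figure for the moderation analysis. Assumed here: two-sided alpha 0.05, no effect of MBI, no effect of dosage, and a correlation r between dosage and outcome change that arises only through motivation.

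**3. Dose slope within the MBI arm.** By Fisher's z, the chance of significance is about Φ(atanh(r)·√(n − 3) − 1.96), plus a negligible opposite tail. With n = 149, √146 = 12.083.

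- r = 0.1: 0.1003 × 12.083 = 1.212; 1.212 − 1.96 = −0.748; about 23%.
- r = 0.2: 0.2027 × 12.083 = 2.450; 2.450 − 1.96 = 0.490; about 69%.
- r = 0.3: 0.3095 × 12.083 = 3.740; 3.740 − 1.96 = 1.780; about 96%.

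The nominal rate is 5%. Simulation with control dosage coded 0 and no true effect gave 68% at r = 0.2 and 96% at r = 0.3.

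Here r is the correlation of dosage with outcome change. If dosage and change each correlate m with motivation, then r = m². So m = 0.3 gives r = 0.09 (about 19%) and m = 0.5 gives r = 0.25 (about 87%; simulated 86%). Correlations of 0.2 and 0.3 need m of about 0.45 and 0.55.

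**4. Arm-by-dosage interaction, dosage measured in both arms.** The standard error of the difference between two Fisher z values is √(2/146) = 0.117. The table compares this approximation with 4,000 simulated regressions, 149 per arm, with no treatment effect.

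| r in MBI | r in control | Approximation | Simulated |
|---|---|---|---|
| 0.2 | 0.2 | 5% | 4.6% |
| 0.3 | 0.3 | 5% | 4.8% |
| 0.2 | 0.1 | 14% | 14% |
| 0.3 | 0.15 | 27% | 25% |
| 0.2 | 0 | 41% | 41% |
| 0.3 | 0 | 75% | 74% |

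For example, in the fifth row: 0.2027/0.117 = 1.732; 1.732 − 1.96 = −0.228; Φ = 0.41.

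The interaction is inflated only when the correlation differs between arms. When it is equal, the interaction is sound in size but dosage itself remains confounded: with r = 0.2 in both arms, a common dosage term over 298 participants is significant in about 93% of trials.

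**The case against.** The strongest reply is that this is loose wording in one exploratory aim. The Measures section already keeps dosage apart, the Analytic plan never names dosage as a model term, confounders are to be considered, and model detail may sit in an analysis plan that is not shown. Aim 4 also speaks of influence on outcomes, so dosage could be meant only as a correlate. Much of this stands, and it limits the weight of the point. It does not remove it: Aim 4 puts dosage in the same list as the moderators, and as a correlate of outcome it is still confounded.

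A reader might infer more than the documents support, in three ways.

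- **That dosage has no control counterpart, so an interaction cannot be estimated.** Processes are assessed in both conditions, and controls have calls, an app and a route to NRT. The interaction is estimable; the difficulty is that it compares unlike things.
- **That the planned regression will produce a spurious moderation effect.** This is a conditional risk. The 69% and 96% belong to a within-MBI slope, or to control dosage coded 0, and the article specifies neither. With equal correlations in both arms, the interaction holds its nominal rate.
- **That a complier-average effect based on a minimum number of calls solves the problem.** MBI mothers below such a threshold still receive the orientation, printed materials, app, texts and videos, and possibly NRT. Assignment can then act other than through calls, and the exclusion restriction is implausible.

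**Conclusion.** The point holds in limited form. Dosage should not be listed as a moderator, and Aim 4 does not agree with the two Measures sections. A confounded dose association is a real possibility: about 23% to 96% false positives for a within-MBI slope at assumed correlations of 0.1 to 0.3, and from about 5% (equal correlations) to about 74% (0.3 against 0) for the interaction. All correlations are assumptions, since the article gives nothing from which to estimate them. The intention-to-treat comparison, the power calculation and Aims 1 to 3 are untouched. The point should be corrected because the change is cheap and determines what Aim 4 can claim; it does not threaten the trial's main conclusion.

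**What to change.** - Take dosage out of the moderators in Aim 4 and keep the four variables named under Covariates and moderators, at their baseline values.
- Make Aim 4, Covariates and moderators, and Process measures and treatment fidelity agree, with dosage described as a process measure.
- Report any dose-response as an exploratory, non-randomized analysis within an arm, adjusted for baseline predictors of uptake and labeled non-causal.
- Optionally, add a complier-average effect with randomization as the instrument. Define compliance as receipt of any MBI component, not as a call count, and state the exclusion restriction.

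The cost is a few changes of wording and, if the option is taken, one exploratory analysis on data already being collected.
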